# STUDY OBJECTIVES and related endpoints

## Primary Endpoint

| Phase 1: Milligrams of benzodiazepines (oxazepam) used to complete 3 days of detoxification and Actigraph-assessed akathisia and sleep.  Phase 2: Time to ‘relapse’ and amount of alcohol intake during 4 weeks of subsequent outpatient treatment. |
| --- |

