# PROTOCOL SYNOPSIS

| Acute and long-term effects of intranasal oxytocin in alcohol withdrawal and dependence: A prospective randomized parallel group placebo-controlled trial |
| --- |

| Sponsor | [name], St. Olav’s University Hospital |
| --- | --- |
| Phase and study type | Phase III |
| Investigational Medical Product (IMP) (including active comparator and placebo) : | Syntocinon nasal spray and placebo |
| Center: | Lade Addiction Treatment Center, Central Norway Regional Health Authority |
| Study Period: | Estimated date of first patient enrolled: 01.10.2016  Anticipated recruitment period: 12 months  Estimated date of last patient completed: 01.10.2017 |
| Treatment Duration: | 3 days in-patient treatment, followed by 4 weeks outpatient treatment and phone interview at 8 weeks. |
| Follow-up: | 4 weeks follow-up during outpatient treatment, phone interview at 8 weeks. |
| Objectives | The primary aim of the study is to test whether daily intranasal administration of oxytocin is more effective than placebo in decreasing the oxazepam dosages required to control withdrawal symptoms during a 3-day inpatient program of medical detoxification. The secondary aims are: 1) test whether daily intranasal administration of oxytocin is more effective than placebo in decreasing CIWA-Ar scores during the detoxification period; 2) test the effects on therapist- and self-reported withdrawal symptoms, dysphoria and Actigraph-assessed akathisia and sleep during the detoxification period; and 3) test whether daily intranasal self-administration of oxytocin is more effective than placebo on alcohol use measures (time to ‘relapse’ and amount, cravings), quality of sleep and mood states during a subsequent 4 week out-patient follow-up period. |
| Endpoints: | Primary endpoint: Phase 1: Milligrams of benzodiazepines (oxazepam) used to complete 3 days of detoxification and Actigraph-assessed akathisia and sleep. Phase 2: Time to ‘relapse’ and amount of alcohol intake during 4 weeks of subsequent outpatient treatment.  Secondary endpoint: Phase 1: CIWA-Ar-score, effects on therapist- and self-reported withdrawal symptoms, dysphoria, effects on mood, craving, sleep. |
| Study Design: | Double blind, prospective randomized parallel group placebo-controlled trial. |

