## Statistical Analysis

Statistical analysis will be performed by Unit for Applied Research, NTNU.

Descriptive data will be presented as mean ± SD. Dichotomuos outcome variables will be compared using non-parametric test (paired Wilcoxon signed rank test, and McNemar´s test). P-values <0.05 will be considered significant.

0-hypothesis: Oxytocin nasal spray does not differ from placebo in reducing alcohol withdrawal symptoms or decrease craving after detoxification

Primary hypothesis 1: Oxytocin nasal spray can reduce the amount of oxazepam needed to complete 3 days of alcohol detoxification.

Primary hypothesis 2: Oxytocin nasal spray can decrease craving the subsequent 4 weeks after detoxification.

Group comparisons of oxazepam use (measures in mg) at 3 days will be done with student t-test. We will use mixed‐effects regression analyses to examine the change in sleep and actigraph scores from D1 to D3, and changes in anxiety, depression and alcohol use from discharge (D3) to follow-up (D30). Statistics will be performed with per-protocol and intention-to-treat data.Mixed methods take the correlation among repeated measures into account, and they use all available data, thereby lessening concerns about missing data. The basic model will include group (oxytocin, placebo) as the between‐subjects factor and time as the repeated measure. The treatment effect will be evaluated as the group by time interaction, according to the planned comparisons. Both group and time will be fixed‐effects. Covariates can also be added to the models, in order to partial out their effects before evaluating the treatment effects. Follow‐up t‐tests and other post hoc methods will be used to test more time‐ and group‐specific hypotheses. We will test primary hypotheses at the .05 level of significance, but follow‐up and exploratory analyses will be tested at the .01 level of significance.

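### The protocol defines its primary outcome in three conflicting ways, and tests two primary hypotheses at an undivided .05

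*Protocol*

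**What the plan says.** Three parts of the protocol name the primary outcome.

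- **Synopsis, Objectives.** There is one primary aim: whether oxytocin is "more effective than placebo in decreasing the oxazepam dosages required to control withdrawal symptoms". The secondary aims include "Actigraph-assessed akathisia and sleep during the detoxification period; and 3) test whether daily intranasal self-administration of oxytocin is more effective than placebo on alcohol use"; the drinking outcomes named there are time to relapse, amount and cravings.
- **Section 2.1, repeated in the synopsis under Endpoints.** The primary endpoint is "Phase 1: Milligrams of benzodiazepines (oxazepam) used to complete 3 days of detoxification and Actigraph-assessed akathisia and sleep", followed by "Phase 2: Time to ‘relapse’ and amount of alcohol intake during 4 weeks of subsequent outpatient treatment". That makes five outcomes.
- **Section 10.4.** There are two primary hypotheses. The first concerns the amount of oxazepam. The second reads "Primary hypothesis 2: Oxytocin nasal spray can decrease craving the subsequent 4 weeks after detoxification".

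On error control, 10.4 says "We will test primary hypotheses at the .05 level of significance" and sets .01 for follow-up and exploratory analyses. It also carries a general rule that p-values below 0.05 count as significant. On populations it says "Statistics will be performed with per-protocol and intention-to-treat data".

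The sample size in 10.1 rests on oxazepam alone.

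**The concern.** Four of the five primary endpoints in 2.1 are secondary in the Objectives, and both statements stand in the same synopsis. Craving is a primary hypothesis in 10.4, but 2.2 and the synopsis endpoint list have it only as a secondary endpoint of Phase 1. The 4-week craving hypothesis therefore has no matching endpoint.

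The two primary hypotheses are each allowed the full .05, so a 5% error rate does not hold for the claim that the trial succeeded on a primary hypothesis. A favourable result on craving, or on one of the actigraph or drinking outcomes, could be presented as a primary result with some support in the text, even if oxazepam showed nothing.

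There is also a practical effect. Section 9.3 promises full monitoring of the primary endpoint, in the singular, against 20% source verification of the case report form data. Which data get full monitoring depends on which definition governs.

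**Working it through.** **1. The three definitions side by side**

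| Outcome | Objectives | Endpoints / 2.1 | Hypotheses in 10.4 |
|---|---|---|---|
| Oxazepam, mg over 3 days | primary | primary | primary (1) |
| Actigraph akathisia | secondary | primary | not primary |
| Actigraph sleep | secondary | primary | not primary |
| Time to relapse | secondary | primary | not primary |
| Amount of alcohol | secondary | primary | not primary |
| Craving over 4 weeks | secondary | not listed (craving secondary, Phase 1 only) | primary (2) |

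Only oxazepam is primary in every column.

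**2. The plan's own sample size**

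Inputs from 10.1: difference 10 mg, SD about 10 mg, alpha 0.05, power 80%.

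n per arm = 2 × (z for alpha/2 + z for power)² × (SD/difference)² = 2 × (1.960 + 0.842)² × (10/10)² = 15.7, so 16. This matches the plan. A one-sided calculation gives 13, so the sizing is two-sided. The exact t-test calculation gives 16.7, so 17.

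**3. Chance of at least one false primary success**

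For k independent tests at 0.05 the formula is 1 − 0.95^k.

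- Two hypotheses (10.4): 1 − 0.95² = 9.75%.
- Five endpoints (2.1), if each is judged by the general 0.05 rule: 1 − 0.95⁵ = 22.6%.

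The outcomes are probably correlated, and the documents give no correlations. A simulation with no treatment effect (20 per arm, two-sample t-tests, 40,000 replicates per setting) used assumed common correlations:

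| Correlation | Two tests | Five tests |
|---|---|---|
| 0.3 | 9-10% | 21% |
| 0.5 | 9% | 19% |
| 0.7 | 8% | 15% |

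**4. Effect of analysing two populations**

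Suppose a win in either the intention-to-treat or the per-protocol set counts. For a single outcome, with the per-protocol set assumed to be 90%, 80% or 70% of those randomized, the 5% becomes 6.6%, 7.1% or 7.6%. That adds about 2-3 points.

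**5. Power for oxazepam under the remedies**

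Two-sample t-test, standardized difference 10/10 = 1:

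| Primary tests | Alpha for oxazepam | 20 per arm | 16 per arm |
|---|---|---|---|
| One | 0.05 | 86.9% | 78.1% |
| Two, alpha split equally | 0.025 | 79.3% | 68.0% |
| Five, Bonferroni | 0.01 | 67.3% | 53.8% |

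The protocol gives no effect size for any other outcome, so their power cannot be computed.

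**The case against.** The best defence is that oxazepam is plainly the intended primary outcome. It is the sole primary aim, the sole efficacy assessment in the synopsis, the measure of efficacy response in 7.1, the sole basis of 10.1, and the first hypothesis in 10.4 with its own named t-test. This stands. A reader might infer that the deciding result cannot be identified at all, but the weight of the text points to oxazepam. The defect is that 2.1, the synopsis endpoint list and the second hypothesis in 10.4 say otherwise.

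Other stronger readings also fail.

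- **Six primary outcomes, 26.5% (1 − 0.95⁶).** No section sets six. The figure pools the list in 2.1 with the craving hypothesis in 10.4, and these are competing definitions.
- **Every listed endpoint tested at .05.** The .05 level is stated by name only for the primary hypotheses, of which there are two. For the five endpoints it has to be drawn from the general rule. Section 10.4 names no test for time to relapse or craving. It does hold follow-up and exploratory analyses to .01, so it is not without error control.
- **Two populations double the chances.** They overlap heavily, and step 4 shows only a small increase.
- **The null hypothesis concerns something else.** It speaks of withdrawal symptoms and craving and does not name oxazepam. But oxazepam is dosed from withdrawal scores, so the wording is loose and does not point to a different construct.

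A statistical analysis plan that is not shown may give a testing order or a lead population, so their absence here is not itself a fault. Such a plan would still leave the protocol's definitions in conflict, and would have to depart from the undivided .05 written in 10.4.

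**Conclusion.** The point holds as a contradiction between three statements of the primary outcome, together with an undivided .05 for two primary hypotheses. On the hypotheses in 10.4, the chance of at least one false primary success is 9.75% if independent and about 8-10% at correlations of 0.3 to 0.7. On the list in 2.1 it is up to 22.6%, or about 15-21%, and only if all five endpoints are tested at the general 0.05 level. The correlations and the per-protocol share are assumptions. The sample size is not in error: it reproduces, and it covers oxazepam only. In a trial described as phase III, the protocol should be reconciled before results are unblinded.

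**What to change.** Make total oxazepam (mg) over the 3-day detoxification, in the intention-to-treat population, the single primary endpoint at two-sided 0.05, and say so identically in the synopsis, 2.1 and 10.4. This agrees with the primary aim, the efficacy assessment and the sample size. Move akathisia, sleep, time to relapse, amount of alcohol and craving to secondary. Word the null hypothesis in terms of oxazepam. Label the per-protocol analysis supportive.

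The cost is an amendment, which under 11.3 needs approval by the authority and the ethics committee. The trial registration described in 12.2 would have to agree with it. The other outcomes lose the primary label, but the trial was not sized for them. No patients are added, and power for oxazepam stays about 87% if all 40 are evaluable.

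Keeping one primary outcome per phase is a workable alternative. The alpha must then be split or the tests ordered, and the endpoint list and hypotheses must name the same outcomes. With an equal split, power for oxazepam is about 79% at alpha 0.025, again with all 40 evaluable and close to the planned 80%.

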## Secondary Endpoints

Phase 1: Test whether daily intranasal administration of oxytocin is more effective than placebo in decreasing CIWA-Ar scores, effects on therapist- and self-reported withdrawal symptoms, effects on mood, craving, sleep.

# Overall STUDY Design

The study is a phase III.

Double blind, prospective randomized parallel group placebo-controlled trial.

4 weeks outpatient treatment

Day 1-3: In-patient

treatment

On admission

____________________________________________________________________________________________
Main assessments Study entry Discharge Follow-up
 D0 D2 D3 D30 + D60

Arm 2:Placebo

Arm 1: Oxytocin

| Study Period | Estimated date of first patient enrolled: 01.10.2016  Anticipated recruitment period: 12 months  Estimated date of last patient completed: 01.10.2017 |
| --- | --- |
| Treatment Duration: | 3 days in-patient treatment, followed by 4 weeks outpatient treatment and a phone interview at 8 weeks. |
| Follow-up: | Check-point at 4 weeks during 4-week outpatient treatment, phone interview at 8 weeks |

# STUDY POPULATION

## Selection of Study Population

The study will be conducted at Lade Addiction Treatment Center, St. Olavs University Hospital, Norway. 40 consecutively admitted in-patients undergoing medical detoxification from alcohol at Lade Addiction Treatment Center will be included in the study.Eligible patients will be identified by the intake team and receive information about the trial together with other standard pre-hospitalization information one week before admittance. Patients admitted on short notice will also be eligible for the study. The randomization will be administrated electronically by the Unit of Applied Clinical Research at the Norwegian University of Science and Technology.

## Number of Patients

40 patients will be included in this trial.

## Inclusion Criteria

All of the following conditions must apply to the prospective patient at screening prior to receiving study agent (e.g.):

- At least one prior episode 2 days or longer in duration during which the subject experienced withdrawal symptoms that caused significant incapacitation (e.g., inability to work or do normal activities) OR at least one prior inpatient or outpatient medical detoxification during which the subject exhibited withdrawal symptoms of sufficient magnitude that sedative-hypnotic or anticonvulsant medication was required at least once on 2 consecutive days after cessation of or reduction in the use of alcohol following 2 weeks or more of heavy daily consumption
- Average consumption of 8-30 standard drinks per day for at least 2 weeks prior to enrollment in the study
- Age 18-65
- Have residency inTrøndelag County after discharge
- Signed informed consent and expected cooperation of the patients for the treatment and follow up must be obtained and documented according to ICH GCP, and national/local regulations.

## Exclusion Criteria

Patients will be excluded from the study if they meet any of the following criteria:

- No alcohol in the blood and more than 15 h since last intake of alcohol at admission
- Adverse reactions to some of the ingredients of Syntoinon nasal spray, e.g. allergic reactions to methyl- and propylparahydroksybenzoat (E 216, E 218) or hereditary fructose intolerance
- Chronic treatment with sedative-hypnotic medications such as benzodiazepines or z-hypnotica
- Dependence on substances other than alcohol, nicotine or caffeine
- Inadequately treated, unstable and/or compromising medical or psychiatric conditions
- Low body weight (BMI < 17) or history of anorexia nervosa or bulimia in the past 2 years
- Pregnancy (females at fertile age will undergo pregnancy testing upon admission); parturition or breast-feeding in the past 6 months; females at fertile age not using oral contraceptives or other hormonal conctaceptive products (patch, i.m. depot injections, ring, implant, IUD).
- Inability to read well enough or understand to complete study questionnaires determined by whether the prospective subject can read the consent form without help and correctly answer basic questions about information in the consent form
- Concomitant participation in another medical clinical trial
- Prior inclusion and participation in the same study.
- Any reason why, in the opinion of the investigator, the patient should not participate.

# TREATMENT

For this study Syntocinon nasal spray is defined as Investigational Medicinal Product (IMP). IMP includes also placebo.

## Drug Identity, Supply and Storage

Syntocinon nasal spray 5 ml is decanted into 10 ml amber glass intranasal spray bottles. The same glass bottles will be used for placebo. Unopened (decanted Syntocinon or manufactured placebo) nasal sprays are to be stored chilled, after opening to be stored in room-temperature. A bottle should be used within 1 month after opening.

**IMP and placebo**

The company Sanivo Pharma AS, previously known as Farmaholding (www.farmaholding.no) will decanter Syntocinon into 10 ml amber glass bottles. The company will also manufacture placebo in identical bottles. The study drug will be decanted to new nasal spray containers, following a Class D regimen. Since the production of placebo and the production of Syntocinon take place in two different locations, testing of absence of oxytocin is considered to be unnecessary.

**The glass bottle and nasal spray pump**

The nasal spray bottles are 10 ml snap-on vials manufactured by Gerresheimer Chalon, France ([www.Gerresheimer.com](http://www.Gerresheimer.com)). They are used for nasal sprays manufactured by GSK, Merck, Sanofi, Abbott and others. The nasal spray pumps are manufactured by Aeropump ([www.aeropump.de](http://www.aeropump.de)). They are currently in use for the following drugs internationally: Nasivin (Merck), Olynth (Pfizer), Iliadin (Merck), Mar Plus (Stada) and Prevalin (Teva). In Sweden they are also used for Nozoil (Trimb) and Renässans (Maxmedica). Both glass bottles and nasal spray pump are provided by Wirth Emballage ([www.wirth.se](http://www.wirth.se)).

**Testing of pH and microbiological testing**

Testing will be performed on both decanted oxytocin and placebo after manufacturing at Sanivo Pharma AS. The pH will be tested by means of a pH-meter. Microbiological testing will be performed according to Ph Eur 2.6.12: Microbiological examination of non-sterile products. Microbial enumeration tests. According to Ph Eur 5.1.4: Microbiological quality of non-sterile pharmaceutical preparations and substances for pharmaceutical use: Nasal use:

• Total aerobic microbial count (TAMC): Max 200 cfu/mL

• Total yeast/mold count (TYMC): Max 20 cfu/mL

• Staph aureus: absence in 1 mL

• Pseudomonas aeruginosa: absence in 1 mL

**Nasal spray pump and depositon**

A specification on the pump system, including the dip-tube and actuator is attached, see appendix A. The actuator has not been modified for this study. Deposition of drug in actuator is not considered relevant, since priming before use will clean the actuator for possible residues from earlier use. After longer periods without use, parts of the fluid could flow back to the bottle and be replaced by air in the pump system, but our instructions for priming immediately before each administration of the spray will handle this situation as well.

**Adsorption to plastic materials in nasal spray pump**

Regarding the possible risk of adsorption of oxytocin to plastic materials in the bottle/pump, the following considerations have been made: The bottle is made of glass, to which there is no risk of adsorption. The pump consists of the plastic materials polypropylene (PP), polyethylene (PE) and poloxymethylene (POM). We have not found any studies on the adsorption of oxytocin to these (or other) plastic materials. We have also checked for studies on the closely related polypeptide vasopressin (which also consists of 9 amino acids, only two of which differ from those of oxytocin), but there were no studies on this hormone either. However, for another peptide hormone, insulin, numerous studies have been performed on adsorption to plastic materials. These studies show that there is no risk of adsorption to materials like PP, but that adsorption to polyvinylchloride (PVC) takes place ^19,20^. Our pump does not contain PVC. Moreover, the surface area of the plastic material in the pump is considerably lower and the time period that the drug delivered to the patient is in contact with the surface of the pump system is considerably shorter that in insulin delivery systems. Taken together, these data indicate that there will not be any significant adsorption to the plastic materials affecting the oxytocin dose delivered to the patient.

To ensure that there is no significant deposistion or adsorption of oxytocin in the spray mechanism or bottle, additional testing will be performed when the production starts. The amount of oxytocin present in the first spray of decanted Syntocinon (immediately after 5 priming sprays) is measured and repeated after 1 month of storage (immedialtely after 1-3 priming sprays as needed) on two bottles of decanted Syntocinon to see if there is loss of active ingredient when the solution is in contact with the plastic parts of the nasal spray pump.

## Dosage and Drug Administration

Information on spray pattern and distribution provided by the trade agency company is attached in appendix A.

Phase 1: 3-day detoxification with 1 dose x 2 daily. Each test dose consists of 6 insufflations of Syntocinon Spray or placebo, with each insufflation given 15 sec apart and alternating between nostrils. Each insufflation consists of 6.7 μg oxytocin.The first intranasal dose of the test substances will be administrated immediately after group allocation. Patients are given instruction in proper intranasal self-administration techniques during their first dose. Instructions of priming and use is also noted in the notebook the participants are given. The second dose is taken at 1800h on admission day. The following two days (day 2-3) the patients will take their intranasal doses at 0900h and at 1800h under supervision. Patients will also be wearing an actigraph during detoxification which will register akathisia and sleep in an inpatient setting.

Phase 2: Patients completing the 3 day oxytocin or placebo detoxification trial, are discharged to a 4 week trial of self-administrated intranasal spray (as needed), with maximum use 2 insufflations x 3 daily in order to reduce alcohol cravings or consumption. Staff and patients will be instructed in priming the nasal spray by completing 5 test sprays before first use as well as 1-3 sprays later on, before administering the spray.

The following specific instructions will be given to the staff and the patients^21^:

1. Use the head upright position in standard practice but allow patients to choose the most comfortable position for themselves.

2. Do not administer if the nose is heavily congested and clear the nose from obvious obstruction before administering.

3. Ensure the bottle is primed. To do so, complete 1-3 test sprays as needed before each dose, until a fine mist can be seen and the spray is ready for use.

4. Close one nostril with one finger while administering the spray to the other nostril. Upon delivery of the medication, inhale and breathe in lightly.

5. Insert bottle 1 cm into the nostril and encourage an administration vertically into the nostril.

6. Alternate administrations between nostrils, 15 seconds between each spray.

7. Keep dust cap on whenever nasal spray is not in use.

Both the staff and the patients will be given hands-on training related to this procedure before administration of the product.

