### Withdrawal Visit

If the patient is withdrawn from the study before completing the study by his/her own will, 3 attempts to reach subject for is made (e.g telephone, mail).Patients withdrawing from the study will go back to standard procedures for the follow-up treatment at Lade Behandlingssenter. Because of no expected side effects and the short half-life of oxytocin, no further examinations or tests are considered needed. The nasal sprays are to be returned to Lade Behandlingssenter.

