## Population for Analysis

The following populations will be considered for the analyses:

- Intention to treat (ITT) population: Includes all randomized participants, regardless of protocol adherence.
- Per-protocol population (PP): Includes all randomized participants showing full protocol adherence.
- Safety population: Includes all subjects who have received at least one dose of study medication. Subjects who withdraw from the study will be included in the safety analysis. A list of withdrawn subjects, preferably with the reasons for withdrawal, will be made.

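### Drinking follow-up is not required for patients who leave the 3-day detoxification early, so the promised all-randomised analysis of the Phase 2 endpoints is not secured

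*Protocol*

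**What the plan says.** Allocation happens once, at the start of the inpatient stay: "The first intranasal dose of the test substances will be administrated immediately after group allocation" (Protocol, Dosage and Drug Administration). The same section sets the condition for the outpatient phase: "Patients completing the 3 day oxytocin or placebo detoxification trial, are discharged to a 4 week trial" of self-administered spray. The Phase 2 primary endpoint is "Time to ‘relapse’ and amount of alcohol intake during 4 weeks of subsequent outpatient treatment" (Primary Endpoint).

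The intention-to-treat population "Includes all randomized participants, regardless of protocol adherence" (Population for Analysis), and "Statistics will be performed with per-protocol and intention-to-treat data" (Statistical Analysis). Neither analysis is named as the main one.

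Three sections deal with patients who leave:

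- Criteria for Patient Discontinuation allows removal from treatment and assessments together. The listed reasons include non-compliance and major protocol deviation.
- Withdrawal Visit provides three contact attempts but says "no further examinations or tests are considered needed".
- Patient Discontinuation offers a final assessment, at a visit or by phone, only where it can be done. It replaces only patients who leave before treatment starts.

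**The concern.** Completing detoxification is decided after randomisation, and treatment may affect it. The protocol's own rationale is that oxytocin eases withdrawal, craving and tension, all plausible reasons for staying or leaving. Exits for safety, deterioration or non-compliance may also differ by arm.

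If drinking is recorded mainly for patients who complete, an analysis labelled intention-to-treat is close to a completer analysis. Suppose oxytocin keeps more high-risk patients in treatment. Its Phase 2 group then contains more people likely to relapse, and a real benefit is understated. If oxytocin instead drives people out, harm is understated. An analysis plan written later can choose an estimand or an imputation method, but it cannot recover drinking data that nobody was asked to collect.

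**Working it through.** **The plan's own figure.** The only sample-size calculation concerns oxazepam (Determination of Sample Size): difference 10 mg, SD 10 mg, alpha 0.05, power 80%. Taken as two-sided, n per group = 2 × (1.960 + 0.842)² × (10/10)² = 15.7, so 16, as stated. It does not bear on Phase 2, which has no calculation. The total of 40 against 2 × 16 = 32 would absorb a 20% loss (32/40 = 0.80), but the protocol states no drop-out or completion rate.

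**Can the all-randomised analysis be supplied with data?** Take a patient who leaves on D2.

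1. *Population.* The patient has been randomised and dosed, so is in the intention-to-treat set and is not replaced.
2. *Drinking data.* In the Flow Chart, Time-Line Follow-back, days to relapse and daily quantity appear only at D30. The notebook is handed out at discharge on D3 (During Treatment, D1-D3). The D60 phone interview asks about the preceding 30 days, so it looks mostly beyond the 4-week window.
3. *Obligation to collect.* There is none. Assessments may be ended with treatment, no tests are required after withdrawal, and the final assessment is conditional.
4. *Model.* The alcohol-use model runs from discharge (D3) to D30 on available data. A patient who is not reached contributes no outcome at all.
5. *Endpoint wording.* The endpoint concerns "amount of alcohol intake during 4 weeks of subsequent outpatient treatment", which this patient never starts. No rule says how the patient counts.

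Steps 1 and 3 are the mismatch. The population ignores adherence, while the discontinuation rules let non-adherence end data collection.

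**Size, simple illustration (all inputs assumed).** Take 20 per arm with true relapse 12/20 in both. Four placebo patients and one oxytocin patient leave early, and all five relapse.

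- Placebo completers: (12 − 4)/(20 − 4) = 8/16 = 50.0%
- Oxytocin completers: (12 − 1)/(20 − 1) = 11/19 = 57.9%
- Apparent difference: 7.9 points against oxytocin, when the truth is 0
- Standard error: √(0.500 × 0.500/16 + 0.579 × 0.421/19) = 0.169, about 17 points

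The shift is about half a standard error, in a scenario chosen to be strong.

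**Size, graded scenarios (all inputs assumed).** Severity U is standard normal. The log-odds of completing fall by 0.5 to 2 per SD of U. The outcome correlates 0.3 to 0.5 with U, and the true effect is zero. Bias = correlation × (mean U in oxytocin completers − mean U in placebo completers). Standard error = √(1/n₁ + 1/n₂), with n₁ and n₂ the completers.

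| Completion, oxytocin / placebo | Bias (SD) | Type I error |
|---|---|---|
| 90% / 90% | 0 | 5.0% |
| 95% / 85% | 0.01 to 0.06 | 5.0 to 5.4% |
| 95% / 75% | 0.03 to 0.12 | 5.1 to 6.4% |
| 90% / 70% | 0.03 to 0.12 | 5.1 to 6.2% |

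Worst case by hand: 19 and 15 completers give a standard error of √(1/19 + 1/15) = 0.345. Bias 0.121 is then 0.35 standard errors, and the two-sided error is P(Z > 1.61) + P(Z < −2.31) = 0.054 + 0.010 = 0.064.

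**The case against.** A reader might infer that the protocol plans to compare completers, so that Phase 2 sets self-selected groups against each other. The documents do not support that. The entry sentence is a treatment rule in the dosing section, and no section limits the Phase 2 comparison to completers. Intention-to-treat is prescribed alongside per-protocol. Patients keep their randomised arm, and several exits are the investigator's decision.

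A reader might also infer that an early leaver's relapse is always lost. It is not. A patient who is reached for the end-of-study assessment would have Time-Line Follow-back over the previous 30 days. That covers drinking on the evening of D2, even from the latest permitted visit day (32 − 30 = 2).

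The statement that no further tests are needed gives side effects and half-life as its reasons. It is a safety judgement, not a decision to forgo efficacy data. How early leavers count, the time origin and the ranking of populations may also sit in a statistical analysis plan that is not shown.

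These points stand, and they narrow the concern. They do not remove it: reaching the patient is optional, assessments may be ended for non-adherence, and no section restores drinking follow-up.

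**Conclusion.** The point holds as a gap between the promised analysis and the data collection that should support it. For time to relapse and alcohol intake, the all-randomised analysis would in practice rest mainly on completers. Bias is a risk, not a certainty, because it needs completion, or the reasons for leaving, to differ by arm over three supervised inpatient days. Its size cannot be derived from the protocol.

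Under the assumed scenarios it is modest, at most about 0.12 SD with type I error 6.4%, and zero when completion and selection are the same in both arms. Those scenarios link leaving to drinking only through severity. Patients who leave in order to drink would make the link stronger, and with about 20 per arm a few of them can move the estimate. The change should be made because it is cheap and because analysis cannot supply the missing data afterwards.

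**What to change.** Leave the entry rule for home spray as it is. Reconcile Withdrawal Visit, Criteria for Patient Discontinuation and Patient Discontinuation with Population for Analysis, as follows:

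- State that stopping the spray or leaving detoxification early does not end drinking follow-up unless the patient withdraws consent to it.
- Collect Time-Line Follow-back at D30, at the visit or by phone, and make the D60 call for every randomised patient.
- Count time to relapse from randomisation or from a fixed study day common to all. Do not start the clock at early departure, since treatment may affect when that occurs. Make the look-back reach the chosen day: from D32, 30 days reaches only D2.
- Make the all-randomised comparison the main Phase 2 result and the completer comparison supportive.

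The last two items could be placed in a statistical analysis plan. The first two must be in the protocol.

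The cost is protocol wording and a few extra phone interviews with instruments already in use. The estimated effect is slightly diluted by patients who never had home spray. No sample-size figure changes.
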